## Abstract

**Background:**

Chronic Obstructive Pulmonary Disease (COPD) is a leading cause of disability, hospitalization, and premature mortality. General practice is well placed to diagnose and manage COPD, but there is a significant gap between evidence and current practice, with a low level of awareness and implementation of clinical practice guidelines. Under-diagnosis of COPD is a world-wide problem, limiting the benefit that could potentially be achieved through early intervention strategies such as smoking cessation, dietary advice, and exercise. General practice is moving towards more structured chronic disease management, and the increasing involvement of practice nurses in delivering chronic care.

**Design:**

A pragmatic cluster randomised trial will test the hypothesis that intervention by a practice nurse-general practitioner (GP) team leads to improved health-related quality of life and greater adherence with clinical practice guidelines for patients with newly-diagnosed COPD, compared with usual care. Forty general practices in greater metropolitan Sydney Australia will be recruited to identify patients at risk of COPD and invite them to attend a case finding appointment. Practices will be randomised to deliver either practice nurse-GP partnership care, or usual care, to patients newly-diagnosed with COPD.

The active intervention will involve the practice nurse and GP working in partnership with the patient in developing and implementing a care plan involving (as appropriate), smoking cessation, immunisation, pulmonary rehabilitation, medication review, assessment and correction of inhaler technique, nutritional advice, management of psycho-social issues, patient education, and management of co-morbidities.

The primary outcome measure is health-related quality of life, assessed with the St George’s Respiratory Questionnaire 12 months after diagnosis. Secondary outcome measures include validated disease-specific and general health related quality of life measures, smoking and immunisation status, medications, inhaler technique, and lung function. Outcomes will be assessed by project officers blinded to patients’ randomization groups.

**Discussion:**

This study will use proven case-finding methods to identify patients with undiagnosed COPD in general practice, where improved care has the potential for substantial benefit in health and healthcare utilization. The study provides the capacity to trial a new model of team-based assessment and management of newly diagnosed COPD in Australian primary care.

**Trial registration:**

ACTRN12610000592044\

## Background

Chronic obstructive pulmonary disease (COPD) is a leading cause of morbidity and mortality [1], ranked globally in 2002 as the fifth leading cause of death [2] and the seventh leading cause of disease burden after ischaemic heart disease and stroke. In Australia, COPD is the fourth leading cause of death for males (4.2% of all deaths) and the sixth leading cause of death for women (3.3% of all deaths); it is also a contributory cause of death in many patients with coronary heart disease or cancer [3]. In the Burden Of Obstructive Lung Disease survey (BOLD), the prevalence of airflow limitation (GOLD Stage II or higher) in Australians aged ≥40 years was 10.8% [4], whereas the prevalence of doctor-diagnosed COPD in the same population was 5.9% [5].

Clinically, COPD is characterised by airflow limitation that is not fully reversible, and is associated with an enhanced chronic inflammatory response to noxious particles or gases [6]. Patients typically present with breathlessness, cough, and sputum production. The most important cause in developed countries is cigarette smoking, and up to 50% of smokers may eventually develop clinically significant COPD [7].

Even mild to moderate COPD is associated with impaired health status [8]. Patients with COPD have increased healthcare utilisation before diagnosis, raising the possibility that earlier diagnosis may allow more rational and directed use of healthcare resources [9]. The feasibility of a COPD case-finding approach has been established. For example, in an Australian study in 2007, 20% of patients identified as being at risk of COPD responded to invitations to be screened and of these 20% had a new diagnosis of COPD on spirometric criteria [10]. This is similar to findings from primary care studies in other countries [11-13]. For diagnosis of COPD, spirometry is required [6], and standards have been developed for the performance of spirometry in primary care [14]. Practice nurses can feasibly and successfully undertake spirometry [13,15]; as for other health professionals, approximately six hours of training are required [16].

Clinical practice guidelines have been developed and disseminated for the diagnosis and management of COPD [6], including in Australia (COPD-X guidelines) [17]. Despite the high level evidence for the efficacy of guidelines-based interventions, the care provided for patients with COPD in community settings indicates low levels of awareness and implementation of these guidelines [18]. Medication use is often not in accordance with guidelines [19,20], and a high proportion of patients prescribed inhalers use them incorrectly [21,22].

Effective treatment for COPD improves symptoms, prognosis, and quality of life. Smoking cessation is the most effective measure to reduce progression of the disease [23]. Because smoking cessation may become less effective at altering the course of disease in patients with severe COPD, interventions that target patients with mild and moderate disease may be more effective [24]. In the Lung Health Study [25] smokers with early COPD who were assigned to a smoking cessation intervention had fewer respiratory symptoms after five years follow-up than those who were not. Smokers diagnosed with COPD [26] or who are told their ‘lung age’ [27] may be more likely to cease smoking.

General practice is well placed to diagnose COPD and provide early intervention and longer-term management [28,29]. Care planning and a team approach are effective in the management of chronic disease. Care planning by general practitioners (GPs) has been shown to improve the clinical outcomes for other chronic diseases such as diabetes [30] and asthma [31], but GPs need more support to develop and implement multidisciplinary care plans [32,33] Current guidelines recommend the use of multidisciplinary care plans in the management of patients with COPD [17].

Practice nurses are increasingly contributing to chronic disease management. Specialised nurses have contributed to the care of patients with diabetes and COPD, and there is evidence of improvements in patient self-care, quality of life, and satisfaction [34]. A Cochrane review [35] of nursing outreach programs for COPD found significant gains in health-related quality of life for patients with moderate COPD, but the review highlighted the lack of high quality studies and concluded that further study was required.

While the role of specialist nurses in contributing to the care of patients with COPD has been examined [35-37] and some evidence of benefit in disease-specific quality of life has been found, there are few studies examining the potential role of practice nurses working in partnership with GPs in providing more coordinated, integrated, and evidence-based care for patients with newly-diagnosed COPD.

### Study aims

The primary aim is to assess the effectiveness of early intervention by a GP-nurse team applying evidence-based guidelines, compared with usual care, in the assessment and management of patients newly diagnosed with COPD. Secondary aims are to assess the acceptability of the two management approaches to GPs, nurses and patients, and to assess the utility of the COPD Diagnostic Questionnaire (CDQ) and COPD Assessment Test (CAT) in an Australian population.

### Study hypothesis

The study hypothesizes that intervention by a GP-practice nurse team leads to improved health-related quality of life and greater adherence with clinical practice guidelines for patients with newly-diagnosed COPD, compared with usual care.

## Methods

### Study approvals

The PELICAN study (Primary care EarLy Intervention for Copd mANagement) is a pragmatic cluster randomized controlled study with two treatment arms, which is being conducted in greater metropolitan Sydney, Australia. The study is funded by the National Health and Medical Research Council of Australia (Project Grant No. 630421). Ethical approval has been obtained from the Human Research Ethics Committee, University of New South Wales (HREC 10015). The project has been registered with the Australian Clinical Trials Registry (ACTRN12610000592044).

### Study design

This pragmatic cluster randomized controlled trial will test the hypothesis that early intervention by a practice nurse-GP partnership will improve outcomes for patients newly diagnosed with COPD, compared with usual care. Because the intervention involves a team approach by treating practitioners, randomization will occur at the practice level rather than at the level of individual patients (CONSORT guidelines for cluster trials [38,39]). All participating practices will use case-finding methods to identify a cohort of patients with newly diagnosed COPD.

The research plan, identifying recruitment strategies, randomization, data collection points, and the relationships between intervention and control groups in the two arms are summarised in Figure 1. Because it is a complex intervention with potential for variable implementation, there will be a focus on process evaluation as well as quantitative outcome measures.

**Figure 1 F1:**
[figure not shown]
Study and data collection processes.

### Inclusion criteria

#### GPs and practice nurses

Practices will be eligible to participate if they have computer-based patient records, employ at least one practice nurse, and have a spirometer. More than one GP per practice may be involved in the study. Written informed consent will be obtained from GP(s) and practice nurse(s).

#### Patients

Patients will be eligible for inclusion if they have attended the practice at least twice, with at least one visit in the preceding 12 months, and have risk factors for COPD (aged 40 to 85, and with a documented history of smoking). Patients will be excluded if they have a recorded diagnosis of COPD, are unable to understand English sufficiently to complete study questionnaires or procedures, or have cognitive impairment.

### Randomization and allocation concealment

Practices will be randomized to deliver either a practice nurse-GP team management approach, or usual care, to patients with newly-diagnosed COPD. Randomization will be undertaken after the nurses have completed spirometry and case-finding training, and before case-management training for the intervention group. Randomization will be carried out independently of study and practice staff by a statistician separate to the study team using a computer-generated randomization program, with a minimisation algorithm to ensure a balance of practice characteristics that could potentially affect study outcomes. These characteristics are: practice size, as indicated by the number of practice nurses (1 or >1); socio-economic status, classified according to Socio-Economic Indexes for Areas (SEIFA, [40]) (low: SEIFA 1-5, high: SEIFA 6-10); and participation by the GP in significant (>6 hours) COPD education activities within the last six months (yes or no). Allocation concealment will be ensured as group allocation will be conducted at the same time as randomization. Practices will be informed about their group allocation by fax.

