#### Data analysis

Data collation will be managed using Access, and data analysis undertaken using the Statistical Package for the Social Sciences (SPSS) by a statistician blind to group allocation. Analysis will be by intention to treat, i.e., by the diagnosis assigned by the practice nurse/GP on the basis of case-finding spirometry, including patients whose diagnosis of COPD is not confirmed by the project officer. Intra-cluster (practice) correlation coefficients will be determined and published for all primary outcome variables to assist future research.

The effect of the intervention on outcomes measured on a continuous scale (such as SGRQ score) will be estimated and tested using mixed model analysis of variance in which time and treatment group will be fixed effects and GP practice and subject nested within practice will be random effects. The effect of the intervention on the dichotomous variables (such as smoking and vaccination status) will be analysed using generalised estimating equations with a logistic link and a model structure that is analogous to that described above.

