#### Sample size calculations

The sample size calculation is based on a minimum clinically important difference for the primary outcome measure (SGRQ) of 4.0 [52], between subject standard deviation in SGRQ of 13 in a similar population [54], intra-cluster correlation coefficient of 0.01, and a resultant design effect of 1.09 for a cluster size of 10. With this design effect, a sample size of 200 patients completing each arm will provide >80% power to detect a difference of 4 or greater in SGRQ (calculations in PASS software). Forty practices will each invite 300 patients to attend a case-finding appointment, and within each practice this is expected to produce 12 patients with a new diagnosis of COPD; loss to follow-up of 20% by 12 months has been assumed. The projected recruitment rate is derived from the response rate to invitation (25%), and the yield of new diagnoses (21%) in our recently completed case-finding project [10].

This sample size will also confer 90% power to identify a doubling of the expected rate of correct inhaler use (from 20% to 40%) at a significance level of 5% (based on an ICCC of 0.1, and design effect of 2.1).

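### The three minimisation factors are missing from the stated analysis models; standard errors are somewhat too large, though the loss for SGRQ is small on the protocol's own inputs

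*Protocol article*

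**What the plan says.** Under Randomization and allocation concealment, the protocol article describes computer-generated allocation of practices "with a minimisation algorithm to ensure a balance of practice characteristics that could potentially affect study outcomes". It names three binary factors:

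- practice size, as one practice nurse or more than one;
- socio-economic status of the area ("low: SEIFA 1-5, high: SEIFA 6-10");
- whether the GP took part in more than six hours of COPD education in the last six months.

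Under Data analysis, the model for continuous outcomes, with SGRQ as the example, is a mixed model "in which time and treatment group will be fixed effects and GP practice and subject nested within practice will be random effects". Dichotomous outcomes are to be analysed by "generalised estimating equations with a logistic link and a model structure that is analogous to that described above". No other section provides for adjustment for the minimisation factors.

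Under Sample size calculations, power rests on a "minimum clinically important difference for the primary outcome measure (SGRQ) of 4.0", an SD of 13, an ICC of 0.01, a cluster size of 10 (design effect 1.09) and 200 completers per arm.

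**The concern.** Minimisation makes the arms alike on the chosen factors, so any outcome differences linked to those factors largely drop out of the treatment comparison. A model without the factors does not know this. It leaves their variation in the practice random effect and counts it in the standard error of the treatment effect. The standard error then exceeds the true sampling error, intervals are too wide and the test rejects too seldom under the null. The treatment estimate itself is not biased.

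What is at stake is precision in a trial of 40 practices, and agreement between the way practices are allocated and the way the data are analysed. The article chose the factors because they might affect outcomes, so its own premise argues for carrying them into the model.

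**Working it through.** **Inputs from the article:** difference 4.0, SD 13, ICC 0.01, cluster size m = 10, 200 completers per arm, 40 practices.

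**Assumptions:** 20 practices per arm (k = 20); two-sided 5% test for SGRQ (5% is stated only with the inhaler calculation); complete balance on the factors. The share f of between-practice variance that the three factors explain is not given, so it is ranged from 0 to 1.

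**1. The stated power.** SE = 13 × √(2 × 1.09 / 200) = 1.357. Power = Φ(4/1.357 − 1.96) = 83.8%. The claim of more than 80% reproduces; about 181 completers per arm would give 80%.

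**2. Variance components.** Between-practice variance is vb = ICC × 169 and within-practice variance is vw = (1 − ICC) × 169. At ICC 0.01, vb = 1.69 and vw = 167.31.

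**3. Formulas.**

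- Model SE without the factors: S0 = √(2(vb + vw/m)/k).
- SE with the factors, which under balance is also the true sampling error of either estimate: S1 = √(2((1 − f)vb + vw/m)/k).
- True type I error without the factors: 2(1 − Φ(1.96 × S0/S1)).
- Power without the factors: Φ((4 − 1.96 × S0)/S1). Power with them: Φ(4/S1 − 1.96).

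Example, ICC 0.01 and f = 1: S0 = √(2 × (1.69 + 16.731)/20) = 1.357; S1 = √(2 × 16.731/20) = 1.293; the ratio is 1.049.

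**4. Results.**

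| ICC | f | S0 | S1 | SE too large by | Type I error without | Power without | Power with |
|---|---|---|---|---|---|---|---|
| 0.01 | 0 | 1.357 | 1.357 | 0% | 5.0% | 83.8% | 83.8% |
| 0.01 | 0.5 | 1.357 | 1.326 | 2.4% | 4.5% | 84.4% | 85.5% |
| 0.01 | 1 | 1.357 | 1.293 | 4.9% | 4.0% | 85.0% | 87.1% |
| 0.05 | 0.5 | 1.565 | 1.424 | 9.9% | 3.1% | 74.4% | 80.2% |
| 0.10 | 0.5 | 1.792 | 1.538 | 16.5% | 2.2% | 62.4% | 73.9% |

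Only the first three rows use the protocol's SGRQ inputs. The ICC of 0.10 is the value the protocol assumes for correct inhaler use. It is shown here on the SGRQ scale to display the mechanism and is not a power figure for the inhaler outcome.

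**5. Simulation check.** Minimisation of 40 practices was simulated 6,000 times per setting. The assumptions were factors at 50% prevalence, a probability of 0.8 for the arm that reduces imbalance, and regression of practice means with t-tests on 38 or 35 degrees of freedom.

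- ICC 0.01, f = 1: type I error 4.4% without and 5.2% with the factors; power 82.8% and 85.0%.
- ICC 0.01, f = 0.5: power 82.6% and 82.9%.
- ICC 0.05, f = 0.5: power 71.4% and 77.9%.
- ICC 0.10, f = 0.5: type I error 3.0% and 4.9%; power 59.5% and 70.6%.

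The direction and rough size agree with the formulas. Levels are slightly lower because degrees of freedom are counted and balance is imperfect.

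**The case against.** The strongest case against has five parts.

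- **Condensed article.** A journal article often leaves covariates to the full protocol or analysis plan, and neither is shown. An unseen plan may add the factors. But the article does more than stay silent: it lists the fixed and random effects term by term, and that list does not match the allocation.
- **The factors may not be prognostic.** The article says only that they could affect outcomes and gives no effect of any of them on SGRQ. This stands. With f = 0 nothing is gained.
- **Repeated measures.** SGRQ is collected at baseline, 6 and 12 months. If the effect were estimated as a change-from-baseline contrast, stable practice differences would largely cancel and the loss would shrink. This also stands, although the stated model names no treatment-by-time term.
- **No validity error.** The test is conservative and the estimate unbiased. This is agreed; the point is one of efficiency and consistency.
- **Adjustment is not free for dichotomous outcomes.** The odds ratio becomes conditional on the factors, and three cluster-level parameters are added to a GEE with 40 clusters. This stands and should be stated with the change.

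A reader might infer something stronger: that a difference of 4 or more SGRQ units between low- and high-SEIFA practices would pull primary power below 80%. The documents do not support this. Two equally common levels that differ by d add (d/2)² to the between-practice variance. At ICC 0.01 and SD 13 the whole of that variance is 1.69, so d cannot exceed 2 × √1.69 = 2.6 units. A larger difference presupposes a larger ICC, and that would be a separate dispute with the sample size inputs.

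**Conclusion.** The mismatch is real: practices are balanced on three factors that the stated models leave out. For SGRQ the consequence is minor on the protocol's own inputs. The standard error is at most 4.9% too large and about 2 points of power are lost, even in the extreme case where the factors explain all between-practice variance. With half explained, the figures are 2.4% and about 1 point. The stated power above 80% is not threatened.

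The point gains weight if the SGRQ ICC proves higher than 0.01, and for outcomes with a higher ICC, such as the 0.1 assumed for inhaler use. Those larger losses rest on assumed values of the ICC and of the share explained, on near-complete balance, and on a treatment main effect rather than a change from baseline. It would be wrong to read the omission as biasing the estimate or inflating the type I error.

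**What to change.** Add the three minimisation factors (practice nurses 1 or >1, SEIFA 1-5 or 6-10, recent GP COPD education yes or no) as fixed practice-level covariates in two places:

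- the mixed model for SGRQ and the other continuous outcomes;
- the GEE for dichotomous outcomes, with a statement that the odds ratio is then conditional on these factors.

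This takes a sentence or two in the analysis section, and the data are already held from randomisation. It costs 3 of 38 practice-level degrees of freedom (40 practices less 2 arms), with no return if the factors prove unrelated to outcome. If the full analysis plan already contains these terms, a statement to that effect is enough.

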### Blinding

Participating GPs, practice nurses and patients will not be blinded to the true aims of the study, nor to their randomization group. Project officers, who will collect study outcome measures, will be blinded to group allocation as will the statistician undertaking the analyses.

#### Intervention and Control Groups: Patient recruitment

For both randomization groups, patient recruitment will involve three stages:

1. Potentially eligible patients, i.e., those at risk of COPD (aged 40 to 85, with documented smoking history) will be identified through a search of the practice electronic records by research assistants and practice staff who have no involvement in patient care.

2. Eligible patients will be recruited by a letter from the practice inviting them to a case-finding visit and management of COPD, if diagnosed. The letter will include a brief description of the research and an invitation to participate, and a response form and reply-paid envelope. Non-responders will be followed up by GP practice staff by telephone.

3. Patients who contact the practice in response to the letter will be given an appointment for the case-finding visit with the practice nurse. The consent form will be signed at the start of the case-finding visit.

For eligible patients who decline to participate in a case-finding visit, basic de-identified information (age, gender, language spoken) will be collected from the practice to allow examination of response bias.

### Training of GPs and practice nurses

#### Intervention and Control Groups—case-finding training of practice nurses for diagnosis of COPD

All practice nurses, before randomization, will receive training in case-finding for diagnosis of COPD. For practice nurses, this comprises a full-day workshop covering the case-finding approach to diagnosis of COPD, and an evening follow-up workshop approximately two weeks later. Because spirometry is essential to the accurate diagnosis and assessment of COPD [6], detailed training in the performance and interpretation of spirometry will be provided (total, eight hours), based on the American Thoracic Society and the European Respiratory Society (ATS/ERS) lung function guidelines of 2005 [41,42]. Nurses will receive practical training on their practice’s own spirometer, and calibration of each spirometer will be checked during the workshop. The follow-up workshop will include revision of spirometry and the processes for the case-finding appointment.

